## **I - RATIONALE**

### **1.1. Cancer biology and targeted therapies**

The management of cancer patients, historically based on histological/clinical diagnostic and prognostic parameters (site, histological type, etc.) and on cytotoxic treatments (chemotherapy, radiotherapy) targeting both cancerous and healthy cells, has made significant progress over the past two decades thanks to increased knowledge of tumor biology. For example, in breast cancer, the analysis of hormone receptors (expression) and the HER2 tyrosine kinase receptor (expression and/or amplification) is now routinely carried out for not only prognosis but also the use of hormone therapy and targeted anti-HER2 therapies (1). Targeted therapies are drugs that can be injected or administered orally that target the signaling pathways that control tumor progression. The toxicity is generally limited. Efficacy is demonstrated in terms of objective response, progression-free survival, and sometimes overall survival, and is all the more important when the targeted protein represents a major and early molecular alteration in the course of the disease (e.g. imatinib that inhibits the mutated Kit receptor in gastrointestinal stromal tumors). These drugs work when the target is present in the disease. This "one target - one drug" concept has been adapted to numerous cancers both in routine clinical practice with around thirty different drugs and in clinical research with several hundred drugs in development.

### **1.2. High-throughput molecular characterization of tumors**

At the molecular level, cancer is characterized by the accumulation and combination of multiple genetic and epigenetic abnormalities responsible for tumor origin, genomic instability, and the acquisition of an invasive and resistant phenotype that results in metastasis and death. For the past fifteen years, high-throughput molecular analyses ("omics") have revolutionized research by making it possible to develop a pan-genomic molecular portrait of a sample (2). The analyses revealed the extraordinary heterogeneity of the tumors and partly explained their histological and clinical heterogeneity. Thus, "organ-specific cancer" is actually comprised of a large number of molecularly distinct diseases that merit individual treatments. Conversely, the cancers of different organs can have identical molecular alterations. This differentiation of cancers and the expansion of the catalog of alterations go hand in hand with the ever-increasing development of innovative targeted therapies. Recently, high-throughput sequencing has revealed a large number of "candidate" mutations (*drivers*) that, while admittedly occurring infrequently (< 5%), are potentially "targetable" by drugs already on the market or in development for the given cancer, other cancers, or other non-cancerous diseases.

### **1.3. Personalized medicine for advanced cancer stages**

In this dynamic context of improved molecular characterization of cancers, development of new targeted therapies, and advances in terms of molecular typing, the therapeutic management must increasingly integrate the specific molecular characteristics of individual tumors. According to the American Food and Drug Administration (FDA), "personalized medicine" aims to obtain "the best medical results by selecting therapeutics according to patient's genomic profile or other patient's characteristics such as proteins, either circulating or at the cell surface". The idea being to deliver treatments based on the molecular typing of the tumor and/or metastasis, regardless of location and histological type, and is currently being applied in research and development. The importance of this approach was demonstrated for the first time by D. Von Hoff's team (3), who used IHC and DNA microarrays to analyze tumor samples from 86 patients with refractory metastatic cancer in order to measure the expression of 61 genes/proteins that were targeted by existing therapies. A potential therapeutic target was detected in 84 patients, 66 of whom then

received the corresponding treatment. For 18 of these, progression-free survival with their treatments lasted more than 1.3 times the length of progression-free survival with previous treatment. The same concept was tested in metastatic breast cancer in the French SAFIR01 trial with promising results. Their analysis of metastatic samples included the search for amplifications in the pan-genome CGH-array and mutations in mTOR pathway (*PI3K*, *PTEN*, *AKT*) genes to see if molecular targets were present that allowed for the referral of the patient to an early trial of targeted therapies. A workable genomic profile was obtained in 64% of patients, 69% of whom had a molecular abnormality of interest for which a targeted drug existed. A targeted personalized treatment was delivered to 43/423 patients with regression or stabilization of the disease of at least 4 months in 13 cases (4). Additional prospective studies are currently underway in France that are testing this concept in patients with all types of metastatic solid tumors: the MOSCATO trial (MOlecular Screening for CANcer Treatment Optimization), sponsored by the Gustave-Roussy Institute; the MOST (My Own Specific Treatment) trial, sponsored by the Léon Bérard Center; and the SHIVA trial, sponsored by the Curie Institute (5). The SHIVA trial plans to evaluate this strategy in a randomized setting for the first time, comparing it to a conventional approach in patients with a molecular abnormality that is potentially targetable by known therapies (imatinib, everolimus, vemurafenib, sorafenib, erlotinib, lapatinib + trastuzumab, dasatinib, tamoxifen, or letrozole). Personalized medicine programs are also underway in several countries: the MD Anderson Cancer Center (6), [name] team in the USA (7), and Toronto in Canada (8). In these studies, typing is performed on a metastatic sample rather than the original tumor due to the appearance of new molecular alterations and resistant clones during tumor progression that may alter therapeutic indications.

#### **1.4. The PERMED01 project**

In this context, the Paoli-Calmettes Institute (IPC) plans to implement the PERMED01 project; a prospective monocentric cohort study collecting clinically annotated tissue samples from patients with advanced solid tumors in order to perform a molecular screening (portrait) of the disease for therapeutic purposes. The IPC has all the necessary knowledge, expertise, and technological tools, particularly in Genomics (9-23), to properly type tumor samples. Our institute has also acquired experience in clinical genomics-based research via three prospective clinical trials, the SA02 trial based on transcriptome analysis and, more recently, the SAFIR01 and Shiva trials. This molecular portrait will complement the research of classical biomarkers (IHC, FISH, sequencing) that has been carried out for years, in addition to providing real-time information on a variety of molecular alterations of interest that could help guide patient treatment.

## **II – OBJECTIVES**

### **2.1 Primary objective**

Define the number of patients whose molecular alteration(s), identified in samples in the context of this study, could lead to the delivery of "targeted" therapy.

### **2.2 Secondary objectives**

- Define the molecular alterations of advanced malignant solid tumors.
- Compare the molecular portraits of metastatic samples with those of the primary tumor if available (heterogeneity, clonal expansion) and normal cells (somatic or constitutional mutations) from the same patient.
- Determine, for the most frequent diseases (such as breast cancer; lung cancer; gynecological cancers, such as cervical, endometrial, ovarian, and fallopian tube; urological cancer, such as prostate, kidney, and bladder; and digestive cancers, such

as colon, pancreatic, and liver), the relationship between these molecular alterations and the histological and clinical disease characteristics, including progression-free survival and overall survival.

- Perform pan-genomic molecular analysis on metastatic samples with full exome sequencing and transcriptome analysis (expression, fusion transcripts: DNA microarray, RNA-seq).
- Perform an analysis of circulating tumor DNA.
- In the case of breast cancer, validate preclinical models of therapeutic tumor response (xenografts, short-term culture, and organoids).
- In cases of breast and digestive cancer, validate the isolation and characterization of circulating tumor cells.

### **III – ELIGIBILITY CRITERIA**

The project is based on the collection and analysis of biological tumor and blood samples for any patient treated at our Institute for advanced malignant solid tumors (metastatic or locally advanced) progressive during at least one line of prior systemic therapy. All cancer types will be included whether they are common or rare cancers for which treatment options are even more limited at an advanced stage.

#### **3.1 Inclusion criteria**

- Age  $\geq$  18 ans.
- Histological cancer diagnosis.
- Locally advanced or metastatic stage, with tumor lesion accessible for biopsy.
- ECOG PS  $\leq$  2 (Appendix 1).
- Affiliated with or benefiting from social security.
- Signed informed consent form for participation in the study.

#### **3.2 Exclusion criteria**

- Person in an emergency situation, an adult who is neither a ward nor a dependent and is not under any type of guardianship or is unable to express consent.
- Progressive brain metastases.
- Brain or bone metastases as the only biopsy site.
- Pregnant or breastfeeding women.

#### **3.3 Patient registration**

Patients after having been informed and accepting to participate in the study shall sign an informed consent form. Eligible patients are registered by completely filling out the inclusion form at:

## **IV – STUDY DESIGN**

### **4.1 Research methodology**

Prospective, open-label, single-center trial.

### **4.2 – Biological sampling at inclusion (cf Appendix 2)**

#### **4.2.1 - Tumor samples (locally advanced tumor or metastasis): biopsies or surgical specimens**

The sampling sites will be determined by the investigative team based on its accessibility and volume. Bone and brain metastases will not be sampled. At least 3 tumor fragments will be taken for each patient and sample site selected.

These fragments will be obtained:

- either via biopsy performed with radiological or endoscopic monitoring in the Radiology Department or the Medical-Surgical Exploration Unit (*Unité d'Explorations Médico-Chirurgicales*), respectively. The sample may be taken, depending on the location of the site selected:

- by percutaneous image-guided biopsy (ultrasound or scanner), mainly using 14, 16, or 18-gauge needles via a manual, semi-automatic, or automatic mechanism. The radiologist will select the most suitable technique and type of needle for each sample.
- by biopsy at the end of an endoscopic ultrasound examination, mainly using 19 or 22 gauge needles that are 8 cm long. Biopsies are obtained by aspiration with a 20 ml syringe with a back-and-forth movement in the tumor; 1 to 3 passes are necessary to obtain a microbiopsy.

The number of biopsy fragments taken will be limited to 5 fragments per target (biopsy site) and the total number of biopsy fragments taken, all targets combined, will be limited to 10 fragments.

- or via surgery performed in the Surgery Department.

The collected fragments will be transferred to the Pathology Department. These will include:

- a fragment to be frozen for storage at the Biological Resources Center (BRC) for the immediate extraction of nucleic acids after verification of tumor cellularity, which will be noted in the report. Only samples with a cellularity greater than 30% will be taken into account. The CRB will be responsible for the storage and extraction of nucleic acids until recovered by the Molecular Oncology and Molecular Oncogenetics laboratories for genomic analysis.
- a fragment fixed and embedded in paraffin will be stored in the Pathology Department for additional immunohistochemical or biological studies.
- at least one fragment to be frozen, after verification of tumor cellularity, for storage in the CRB at -80 °C or in liquid nitrogen (depending on the mode of preservation of the tissue; in a cryotube in nitrogen or a bag at -80 °C) for subsequent proteomic and/or genomic molecular studies.

- specifically, in the cases of patients with locally advanced or metastatic breast cancer and lung cancer: when an additional fragment is available, it will be sent to UMR1068 to be used in an ancillary study validating preclinical therapeutic sensitivity models (xenografts) of locally advanced or metastatic breast tumors (Appendix 3).

In the event that the tumor volume is insufficient to obtain 3 fragments, priority will be given to the fragment intended for the extraction of nucleic acids, followed by the fragment to be fixed and embedded in paraffin. If none of the samples taken allow for the characterization of the tumor's genomic abnormalities, regardless of the stage at which the failure occurs, it will be possible to propose a second biopsy to the patient as long as the inclusion criteria are still met. The decision to take a second sample is at the discretion of the investigator and his team, as is the choice of the metastatic site to sample, which may be the same as or different from the initial sample site.

In the event of a relapse during the follow-up period, the option of proposing a new sampling to the patient for an updated molecular characterization of the tumor is at the discretion of the investigator and his team.

The sample path, from its collection to the Pathology Department, the BRC, and finally the molecular laboratories will be strictly defined and traced for each patient.

#### 4.2.2 – Blood samples

To definitively identify somatic alterations, it is necessary to compare the genome of cancer cells with that of normal cells (e.g. leukocytes) from the same patient. In addition, an analysis of circulating tumor DNA and circulating tumor cells may be performed as part of ancillary studies described in the appendices (Appendices 4 and 5).

For each patient there will be taken, preferably upon inclusion during a check-up, biopsy, or initial visit to an operating room (examination under anesthesia, diagnostic or therapeutic surgical procedure), 5 tubes each with 4 ml of blood in EDTA, i.e. 20 ml of blood for the extraction of DNA from normal cells and analyses of circulating tumor DNA (Appendix 4).

The tubes will be sent to the CRB within 2 hours for centrifugation (at 800G for 10 minutes at 4 °C) and aliquoting (plasma cryotubes for the study of circulating tumor DNA and pellet for DNA extraction) followed by frozen storage. In the event of a relapse during study follow-up, a new blood sample (5 tubes of 4 ml blood in EDTA) may also be taken for analysis of circulating tumor DNA.

Specifically, in cases of patients with breast cancer or cancer of the digestive tract:

As part of the complementary study of circulating tumor cells described in Appendix 5, an additional sample of 5 tubes of 4 ml of blood in EDTA, i.e. an additional 20 ml, will be collected exclusively in patients suffering from locally advanced or metastatic breast cancer or metastatic digestive cancer. The total volume of blood drawn from these patients will be 40 ml.

#### **4.3 – Clinical data**

Clinical data from medical files and existing pathology databases of the IPC that were already declared to the CNIL will be recorded in the Case Report Form (CRF).

The anonymized patient data could also be used for the generation of a data warehouse model aiming to both structure clinical and genomic cancer data and set up a system allowing the data to be shared between the different members of a national group (OSIRIS: a national project model on data sharing and integration launched by the Integrated Cancer

Research Sites (SIRICs, French comprehensive cancer centers) and accredited by the French National Cancer Institute).

#### **4.4 – Molecular analyses**

The molecular analyses will be carried out by the Molecular Oncology and Molecular Oncogenetics laboratories of the Paoli-Calmettes Institute. Real-time, weekly to bi-monthly analyzes will include testing for DNA copy number alterations and mutations, as well as assessing protein expression. These will concern genes of therapeutic interest that can be targeted by existing drugs or that predict the benefits of a particular systemic treatment. In our experience, it will take between 3 to a maximum of 5 weeks to obtain results (4 weeks in the SHIVA trial for the first 100 patients included). The DNA and RNA will be extracted according to a standard method and their integrity verified on gel and Agilent microarrays.

##### 4.4.1 – Testing for copy number alterations: CGH-array

Gene amplifications and deletions will be identified. Tumor DNA will be hybridized on pangenome arrays for CGH-arrays (244K Agilent Technologies). The choice of microarray may vary depending on technological developments.

##### 4.4.2 – Testing for mutations: targeted next-generation sequencing (NGS)

Mutations in genes of interest (around 370 selected genes, of which nearly 50 are "targetable" by existing drugs) will be identified via targeted next-generation sequencing (NGS). Two different technologies will be used: the PGM Ion Torrent system (Life Technologies) or the MiSeq platform (Illumina), with the HaloPlex kit (Agilent Technologies) including primers for the 370 genes of interest. The relevant medical literature will be monitored during the study in order to complement and update the list of genes coding for proteins of therapeutic interest.

##### 4.4.3 - Validation of protein expression of relevant targets: IHC

Immunohistochemical analysis (IHC) will complement molecular analysis in certain cancers (e.g. hormone receptors and HER2 in breast cancer) and possibly validate the expression of the protein of interest identified via genomic analysis as altered (amplified, mutated). These analyses will be conducted on the fragments fixed and embedded in paraffin in the Pathology Department.

##### 4.4.4 - Bioinformatics analysis of molecular data

The raw files of CGH-array and NGS results will be sent to the Institute's bioinformatics and biostatistics team. The results will then be transmitted in the form of a comprehensive standardized report, which will be recorded in the CRF. The report will be sent to the members of the multidisciplinary molecular tumor board (MTB) for scientific validation before the next meeting. All data generated (molecular analyses, IHC results, etc.) will be stored in a centralized database of the Data Management Unit of the DCRD.

##### 4.4.5 - Complementary molecular analyses.

As part of the secondary objectives of the study, additional molecular analyses will be performed on the remaining tumor DNA, normal DNA, and tumor RNA, such as transcriptome analysis via DNA microarray (24-26) or by RNA-Seq on tumor RNA, or full exome analysis on tumor DNA. Concerning the blood, genomic analyses of circulating tumor DNA will also be performed.

## **4.5 – Patient care**

Patients who are candidates for this project will be given a specialized consultation. During the consultation, the informed consent form will be given to the patient. If the patient agrees to participate in the study (signs consent form), the taking of the samples will be scheduled according to the above description (4.2- biological sampling at inclusion). Once the molecular analyses have been carried out, all the clinical and molecular data will be presented and discussed during a multidisciplinary, weekly, medical/scientific MTB.

This study does not evaluate proposed treatments. Patient care and monitoring will therefore be carried out according to the procedures and practices of the associated center or the specificities of a clinical trial in which the patient could be included, according to the recommendations of the MTB. The patients will then be followed for a period of 3 years. Follow-up data (relapse, death, etc.) will be collected annually. If a cancer susceptibility gene is identified, specific and individualized care will be offered to the patient. This care will not be carried out as part of the study and will require the signing of another specific informed consent form.

## **V – EVALUATION OF SERIOUS ADVERSE EVENTS**

### **5.1 Definition**

Any harmful event occurring in a person participating in biomedical research, whether or not the event is related to the research.

Any event is considered to be a serious adverse event (SAE) if it:

- results in death.
- is life-threatening.
- results in hospitalization of greater than 24 hours or an extension of existing hospitalization.
- causes permanent or a severe temporary disability.
- is the appearance of another cancer.
- causes a birth defect, fetal malformation, or an abortion
- is medically significant.
- is a drug overdose (accidental or intentional).
- is an undesirable clinical or laboratory finding of a serious nature or considered as such by the investigator (with mention of the severity).

**An event is not considered a serious adverse event if it:**

- results in hospitalization of fewer than 24 hours.

- resulted in a hospitalization scheduled prior to inclusion in the study, as well as any medical procedures included as part of the study (hospitalization for placement of an implant, catheter, etc.) insofar as no complications are observed.
- is an adverse event related to the treatment of the disease.
- is any hospitalization or death related to cancer progression and occurring beyond the notification period defined in the protocol.

## 5.2 Definition of expected serious adverse events (E-SAE)

This trial does not evaluate treatments proposed following the multidisciplinary consultation meeting. Events described as related to the sampling conducted for the purpose of this study (blood and tumor samples) will be considered as E-SAEs.

The E-SAEs below will not be reported by the sponsor:

- During blood collection: mild pain, the appearance of a bruise on the arm at the site of the blood sample, "discomfort" felt when using a needle, and exceptional physical discomfort.
- During tumor sampling:
  - Percutaneous samples: very moderate risk of hemorrhage, which may require sutures; an exceptional risk of infection.
  - Endoscopic or surgical samples: risks associated with performing the biopsy or surgery (depending on the site and method of sampling), in particular for an operation.
    - Without general anesthesia: pain, moderate risk of hemorrhage post-sampling; moderate risk of thrombosis post-sampling, exceptional risk of infection, pancreatitis, etc.
    - With general anesthesia: risks associated with surgery and anesthesia including a low risk of perforation, which may involve in-hospital monitoring with antibiotic therapy due to the risk of infection, post-operative pain, nausea, post-sampling hemorrhage, post-sampling thrombosis, and in rare cases sepsis, pneumothorax, and pancreatitis.

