## 5.3 Definition of a suspected unexpected adverse reaction (SUSAR)

A SUSAR is an event whose nature, intensity, and course are at odds with the actions performed in this research.

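### Sections 5.2 and 5.3 judge whether a sampling reaction is expected by two unlinked tests, and 5.2 conflicts with 9.6 on what the sponsor reports

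*Protocol*

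**What the plan says.** **Protocol, 5.2.** After noting that the treatments proposed are not evaluated, the section states: "Events described as related to the sampling conducted for the purpose of this study (blood and tumor samples) will be considered as E-SAEs". It then introduces a list with "The E-SAEs below will not be reported by the sponsor". The tumor-sampling part of the list is split by route:

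- Percutaneous: "Percutaneous samples: very moderate risk of hemorrhage, which may require sutures; an exceptional risk of infection".
- Endoscopic or surgical, without general anesthesia: pain and hemorrhage, then "moderate risk of thrombosis post-sampling, exceptional risk of infection, pancreatitis, etc".
- Endoscopic or surgical, with general anesthesia: among others, "post-sampling thrombosis, and in rare cases sepsis, pneumothorax, and pancreatitis".

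**Protocol, 5.3.** "A SUSAR is an event whose nature, intensity, and course are at odds with the actions performed in this research". The sentence does not mention the 5.2 list.

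**Protocol, 4.2.1.** The first sampling route described is "by percutaneous image-guided biopsy (ultrasound or scanner), mainly using 14, 16, or 18-gauge needles".

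**Protocol, 5.4 and 9.6.** The investigator declares a serious adverse event that occurs within 6 days of a sample, within 24 hours. The sponsor informs the ANSM of serious events probably caused by the research. Neither section exempts expected events.

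**The concern.** Expectedness should be decided by comparing an event with one stated reference, separately from whether the event is thought to be caused by the research. The first sentence of 5.2 merges the two questions, because an event is expected once it is related to sampling. Section 5.3 then asks a different question and points to no reference. The route-specific list could have served as that reference, but its stated role is to mark what the sponsor need not report.

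The site and the sponsor could therefore give the same complication different classes, depending on which sentence each applies. What the sponsor passes on then also depends on whether 5.2 or 9.6 is followed.

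**Working it through.** No arithmetic applies, because the point depends on no rate, count or sample size. The check puts the rules side by side under each possible reading of the first sentence of 5.2.

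**Reading A (literal).** Every event related to study sampling is an E-SAE. The wording that introduces the list favors this reading, since it presents the listed events as a subset of the E-SAEs, the part exempt from sponsor reporting.

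**Reading B (narrow).** Only the events described in the list are E-SAEs.

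| Event related to a study sample | 5.2, reading A | 5.2, reading B | 5.3 | No-report sentence in 5.2 | 9.6, if serious and probably due to the research |
|---|---|---|---|---|---|
| Hemorrhage of the listed extent after percutaneous biopsy | Expected | Expected | Not a SUSAR | Exempt | Inform the ANSM |
| Pneumothorax or thrombosis after percutaneous biopsy | Expected | Not listed | Not settled | Not covered | Inform the ANSM |
| Unlisted reaction unusual in all three features named in 5.3 | Expected | Not listed | SUSAR | Not covered | Inform the ANSM |
| Listed type of event, unusual in intensity only | Expected | Arguable | Literally not a SUSAR, since 5.3 joins the three features with *and* | Arguable | Inform the ANSM |

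Step by step:

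1. Sections 4.5 and 5.2 say that the proposed treatments are not evaluated, so sampling is the only research act to which a reaction can attach. Under reading A no such reaction can be unexpected. Section 5.3 nevertheless provides for unexpected ones, and the third row is then both E-SAE and SUSAR.
2. Under reading B the double classification disappears, but the percutaneous entry becomes decisive. It names hemorrhage and infection and is closed, whereas the entry for endoscopic or surgical sampling without general anesthesia is left open-ended. Thrombosis stands in both endoscopic or surgical entries. Pneumothorax stands only in the one with general anesthesia: "in rare cases sepsis, pneumothorax, and pancreatitis".
3. Under reading B the second row then depends on 5.3. Whether a complication that the protocol itself names for other sampling routes is out of keeping with a percutaneous biopsy is a matter of opinion.
4. In the first row 5.2 exempts the sponsor from reporting. If the event is serious and probably due to the research, 9.6 requires the sponsor to inform the ANSM. This conflict is the same under both readings.

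**The case against.** **The two strongest claims cannot both hold.** A reader might infer that pneumothorax after percutaneous biopsy belongs to no class, and also that no sampling reaction can ever be unexpected. The first needs reading B and the second needs reading A. Under A the event has a class, E-SAE. Under B the SUSAR class is not empty. What stands is that the text does not choose between the readings, and each leaves a defect.

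**Seriousness and causality are not wholly absent from 5.3.** Its body sentence states neither. However, its heading speaks of a suspected reaction, the acronym implies seriousness, and it sits in the section on serious adverse events. This objection stands. The defect in 5.3 is the missing link to a reference list.

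**Events would not be lost.** A reader might infer that real signals from percutaneous sampling could go unseen. Section 5.4 requires declaration whatever the expectedness, and the investigator records the causal relationship to the samples. The no-report sentence covers only listed events, so an unlisted percutaneous complication is not exempt. This stands and limits the harm.

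**No count of affected events is possible.** The protocol gives no split of samples by route, no number of thoracic biopsies and no complication rate. Nor is any comparison of complications by route planned in the objectives or in 6.1, so none is undermined.

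**The gap concerns percutaneous biopsy, not all needle biopsy.** Endoscopic ultrasound sampling also uses needles. It falls under the endoscopic entries, which list thrombosis.

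**A short list of expected events is conservative.** Lengthening the percutaneous entry would make more events expected and, while the no-report sentence stands, exempt more of them. Which complications belong there is a clinical judgment that the documents do not settle. This also stands and shapes the fix.

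**Conclusion.** The concern holds as a defect of wording in the safety section. Sections 5.2 and 5.3 use unlinked tests. Under the literal reading of 5.2, an unusual sampling reaction is both expected and a SUSAR. Under the narrow reading, pneumothorax or thrombosis after a percutaneous biopsy is unlisted and 5.3 does not settle its class. Separately, the no-report sentence in 5.2 conflicts with 9.6.

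The consequence is inconsistent classification and onward reporting, not non-detection. Its size cannot be given in events. Inclusion sampling is planned for up to 560 patients (6.2), with optional second and relapse samples, but the number of percutaneous samples is not stated. The primary objective, the sample size and the planned analyses are unaffected.

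The conclusion rests on the wording alone. The one interpretive step is that a complication named for other routes is not plainly out of keeping with percutaneous sampling. The double classification under the literal reading and the conflict with 9.6 do not depend on that step.

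**What to change.** 1. In 5.2, replace the sentence that makes sampling-related events expected as such. State instead that only events on the list for the route used, at the nature and severity described there, are expected.
2. In 5.3, define a SUSAR as a serious event, suspected to be due to a study sample, whose nature, severity **or** course is not consistent with that list.
3. Reconcile the no-report sentence in 5.2 with the sponsor's duty in 9.6, and keep the question of what is expected apart from the question of what is reported.
4. Have the sponsor reconcile the percutaneous entry with the entries for the other routes. Whether pneumothorax, thrombosis or anything else is added is for the sponsor's clinical judgment. It should be decided together with item 3, so that a longer list does not widen the reporting exemption unnoticed.

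The cost is a few sentences of protocol wording and the matching line on the serious adverse event form. No extra patients or data are needed. The downside is possibly a few more expedited reports.
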